### Outcomes

The primary endpoints of the study are as follows:
The proportion of children showing stunted growth (height-for-age *z*-value < − 2) at 2 years of age to measure the impact of TBST on child developmentMaternal Hb at 24 months after delivery to measure the impact of TBST on maternal health

The secondary endpoints of the study are as follows:
Sensitivity and specificity of the POC-CCA test compared to a panel of reference standard tests (measured as part of the cross-sectional study at non-randomized sites)Women’s health-related quality of life, capacity to work and participate in economic activities and cost-effectiveness of the interventions

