### Sample size and statistical analysis

The sample size was calculated in relation to the primary child outcome proportion showing stunted growth at 2 years of age, for which a larger sample size is assumed to be necessary than for the maternal outcome (Hb, 2 years after delivery).

The prevalence of stunting in Madagascar is estimated to be 40% of children under 2 years of age [26]. For our sample size estimate, it was conservatively assumed that:
Twenty per cent of all children at the age of 2 years are stunted (height-for-age *z*-score < − 2)The intervention can reduce the proportion of stunted children by 50% in infected individuals, i.e. to observe that 10% of all children at the age of 2 years are stunted in the intervention arm.

In order to estimate the appropriate number of infected individuals at 9 months of age, sample sizes with power values of 80% and 90% were subsequently calculated using the OpenEpi tool [27]. For a power of 80%, at least 394 infected individuals at 9 months of age would be required and for a power of 90% 526 individuals. The design effect was assumed to be 1.9 by which the initial sample size needs to be multiplied to account for the clustered design of the study. This leads to a sample size of 749 for 80% power and 1000 for 90% power.

With an annual loss to follow-up of 10% from a visit to visit and an infant mortality rate of 4%, 86% of all mother-infant tandems are expected to present for the 9-month visit. For the 2 years visit, a loss to follow-up of around 10% between 9 months and 2 years is assumed, so that around 0.86 × 0.9 = 77.4% of all mother-infant tandems are expected to present for the 2-year visit. To correct for loss to follow-up, we use the factor 1/0.774 = 1.3. Since our analyses only focus on women infected with schistosomiasis, the number of women to be recruited needs adjusting, considering that the expected prevalence of 0.25 results in an additional inflation factor of 4 leading to an inflation factor of 1.3 × 4 = 5.2.

We hence planned to enrol 4200 eligible pregnant women in the 40 randomized cluster of the trial ensuring a power between 80 and 90% and an additional 1000 participants for the cross-sectional sub-study in the non-randomized sites. Based on the 40 randomized clusters identified for this study, an average of 105 women per cluster is needed to be recruited per cluster.

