### Analysis for the primary outcomes

For the main child endpoint, the proportion of stunted children (height-for-age *z*-value < − 2) at 2 years will be compared between the intervention and control arm using the chi-square tests and *t*-tests. Reference standards from Madagascar as reported by the WHO [28] will be considered in the analysis. For the maternal main endpoint, the difference in Hb 2 years after delivery will be compared between the intervention and control arms using the *t*-tests. For all analyses, a significance level of alpha *=* 0.05 is assumed. Additional analyses will be performed using mixed-effects logistic and linear regression models to account for the between-cluster variation as a random effect. Secondary and other outcomes that are normally distributed will be analysed in the same way.

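### The binary child primary endpoint is given two tests, chi-square and t-test, with no statement of what the t-test is applied to or which test decides.

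*Protocol article*

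**What the plan says.** The Outcomes section of the protocol article defines the child primary endpoint as a binary measure: "The proportion of children showing stunted growth", meaning a height-for-age z below -2, at 2 years. No continuous measure of child growth appears among the primary or secondary endpoints there.

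Under Analysis for the primary outcomes, that proportion "will be compared between the intervention and control arm using the chi-square tests and" t-tests. Maternal haemoglobin, by contrast, is given t-tests only. The section continues "For all analyses, a significance level of alpha" of 0.05 is assumed, with no order among tests. The cluster-level models come afterwards and in a supporting role: "Additional analyses will be performed using mixed-effects logistic and linear regression models". A general sentence follows: "Secondary and other outcomes that are normally distributed will be analysed in the same way". It does not mention height-for-age z.

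Sample size and statistical analysis powers the trial on the proportion. The assumption for planning is "Twenty per cent of all children at the age of 2 years are stunted", reduced so as "to observe that 10% of all children at the age of 2 years are stunted in the intervention arm", with a design effect of 1.9. The same section cites a national stunting prevalence of 40%.

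**The concern.** A primary endpoint needs one deciding test. Here two are named, and the second does not fit the endpoint as defined: a t-test ordinarily compares means of a continuous measure, and none is defined for children. A reader can take it in three ways:

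- a t-test on the individual 0/1 indicator;
- a t-test on the stunting proportions of the 40 clusters;
- a t-test on mean height-for-age z.

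These are not interchangeable. The second respects randomization by health centre, while an individual-level chi-square does not. The third changes the endpoint. The additional mixed models cannot settle a disagreement, because they are not given the deciding role. If the two tests disagree at the end of the trial, the document does not say whether the child endpoint was met.

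**Working it through.** **1. The plan's own figures.** Inputs from the sample size section: 20% versus 10% stunted, 80% and 90% power. Two-sided 0.05 is assumed, since sidedness is not stated. With unpooled variance, n per arm = (z_α/2 + z_β)² [p1(1−p1) + p2(1−p2)] / (p1−p2)².

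- 80%: (1.960 + 0.842)² × (0.16 + 0.09) / 0.01 = 196.2, so 197 per arm, 394 in total.
- 90%: (1.960 + 1.282)² × 0.25 / 0.01 = 262.7, so 263 per arm, 526 in total.

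Both match the article. Multiplying by 1.9 gives 748.6 and 999.4, the stated 749 and 1000. The trial is thus sized on the proportion, and the design effect is part of the plan.

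**2. Reading A: t-test on individual 0/1 data.** In 4,000 simulated trials of 197 per arm at 20% versus 10%, the t-test and the uncorrected chi-square gave the same decision every time. The second test adds nothing.

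**3. Reading B: t-test on cluster proportions.** A test that ignores clustering understates the standard error by √1.9 = 1.378. Its true type I error is 2[1 − Φ(1.960/1.378)] = 2[1 − Φ(1.422)] = 15.5%.

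As a check, I simulated 20 clusters per arm with no treatment effect, beta-binomial counts and the intracluster correlation set so that the design effect is 1.9. Cluster sizes follow from the article: 4200 × 0.774 / 40 = 81 children, or 81 × 0.25 = 20 if only the infected count. There were 20,000 runs per row.

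| Children per cluster | Stunted | Chi-square error | Cluster t-test error | Tests disagree |
|---|---|---|---|---|
| 20 | 20% | 15.6% | 5.0% | 10.6% |
| 20 | 40% | 15.4% | 5.0% | 10.4% |
| 81 | 20% | 15.6% | 5.1% | 10.4% |
| 81 | 40% | 15.5% | 4.9% | 10.6% |

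Under this reading, which test decides is the difference between a valid and an invalid analysis.

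**4. Reading C: t-test on mean z.** The documents give no SD or shape for z, so a normal distribution with a constant shift is an assumption. The share of information kept by cutting at the point where a proportion p is stunted is φ(z_p)² / [p(1−p)].

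| Stunted | Share kept | Mean z relative to cut-off | Null correlation (√share) | Error if either test may decide |
|---|---|---|---|---|
| 10% | 0.342 | 2.92 | 0.585 | 8.8% |
| 20% | 0.280² / 0.16 = 0.490 | 2.04 | 0.700 | 8.3% |
| 40% | 0.386² / 0.24 = 0.622 | 1.61 | 0.789 | 7.9% |

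The last column is the bivariate normal probability that at least one statistic exceeds 1.96 in absolute value, before any effect of clustering.

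**5. What mean z would add.** Under the same assumption, 20% versus 10% is a shift of 1.282 − 0.842 = 0.44 SD. Comparing means would need 164 children in total for 80% power against 394 for the proportion, and 218 against 526 for 90%: a ratio of 2.4. These are before the design effect.

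**The case against.** The fairest defence is that the grammar of the sentence attaches both tests to the proportion. Mean z is not mentioned there, so reading C has the least textual support. The document also contains no rule that either test may decide. Both points stand. A reader might infer that the plan carries an 8.3% error rate, but the text does not support that as a property of the plan. It holds only if the t-test is on mean z and success is claimed on either test.

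A reader might also infer that dichotomizing height-for-age is itself an error. It is not: stunting is a legitimate public-health endpoint, is named consistently throughout, and is what the trial is powered on. Nor does the absence of mean z from the endpoint list show that it will go unanalysed, given the general sentence on other normally distributed outcomes. The efficiency gain is an argument for a cheap addition. It also rests on a uniform shift, whereas the sample size section places the benefit in infected children.

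A third defence is that a separate analysis plan may name the lead test. It may. But this article does specify the primary analysis, and does so with two tests where haemoglobin has one. That is an ambiguous statement, not an omitted detail.

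Finally, simply deleting the t-test would be a poor remedy. Under reading B it would remove the only test in that sentence that respects the clustering and leave the chi-square with its 15% error. The remedy must name a cluster-adjusted test.

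**Conclusion.** The point holds: one binary primary endpoint has two named tests, the t-test's variable and unit are undefined, and nothing says which test decides. The size depends on the reading. It is nil on individual 0/1 data. On cluster proportions it is about 5% against about 15% type I error, at the article's assumed design effect of 1.9. On mean z, with a claim on either test, it is about 8% (7.9% to 8.8% over 40% to 10% stunted) before clustering. The documents do not show which reading is meant, so no single error rate can be assigned to the plan. The information advantage of mean z, 1.6 to 2.9 times and 2.0 at 20% stunted, is a secondary point and depends on an assumed normal shift.

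**What to change.** In Analysis for the primary outcomes, state that the stunting proportion alone decides the child primary endpoint, and that it is tested once, at 0.05, by the mixed-effects logistic model with a random effect for cluster that the section already names. Remove the chi-square and t-test as deciding tests for this endpoint.

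In Outcomes, list mean height-for-age z at 24 months as a secondary child endpoint, analysed with the linear mixed model already named.

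No new data are needed: height is measured for all children at the 24-month visit, and z must be computed to apply the cut-off. The costs are a minor amendment while follow-up is under way (Trial status places the trial at its 9-month visits, with follow-up to autumn 2022) and a wider interval than the naive tests give, by a factor of about √1.9 = 1.4 if the assumed design effect is right. The sample size already allows for that design effect.

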### Randomization

Randomization was done at the CSB level. For randomization, a list with the codes of the 20 CSBs in the regions of Bongolava and Itasy (so-called Antananarivo sites) and 20 CSBs in the region of Amoron’i Mania (so-called Fianarantsoa sites) was provided to the Leiden University Medical Center (LUMC), which randomly allocated 10 of the sites to control and 10 to intervention arm stratified by regions. LUMC informed the University of Antananarivo, University of Fianarantsoa and BNITM about the randomization result.

While blinding at the CSB level is not possible, all procedures of the study and of TBST (including urine sampling) are implemented at both the intervention and control CSBs. Only the actual POC-CCA test and the treatment of positives are exclusively done in intervention sites. In the participant ID, an alphanumeric element will define the recruitment site of the women. In case women would change the study site during the course of the study, the study nurses would be able to identify the non-correspondence of the site from the participant ID. This ensures that the randomization scheme is kept.

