**Table 3 Tab3:**
[figure not shown]
Scheme of scheduled visits. T0 mothers enrolment at 5^th^ or 6^th^ month of pregnancy pregnancy; T1 pre-delivery follow up at the 8^th^ month of pregnancy; T2 delivery follow up at birth and inclusion of children; T3 follow up 9 month after delivery; and, T4 final follow up 24 months after delivery

T0: mother’s enrolment during the 5th or 6th month of pregnancy. Haemoglobin is measured on-site using the Hemocue® system, and a urine sample is being collected (≥ 25 ml). In the TBST intervention arm, the POC-CCA to test for schistosomiasis infection is done on-site. Women who test positive are offered (40 mg/kg) PZQ treatment. Additional samples (Table 4) are being collected at the non-randomized sites for the cross-sectional sub-study to assess the sensitivity and specificity of the POC-CCA test against a panel of reference tests described in Table 4.T1: 1st follow-up, 8th month of pregnancy. Haemoglobin is measured on-site by means of the Hemocue® system.T2: 2nd follow-up, delivery and child enrolment. The case report form (CRF) is completed. The newborns are included, unless the mother decides to withdraw her/him from the study. Weight and height of the newborns are measured.T3: 3rd follow-up, 9 months after delivery/birth. Haemoglobin is measured for all women using the Hemocue® system. Height and weight are measured for all children. A urine sample is being collected (≥ 25 ml) from all mothers and children. In the TBST intervention arm, the POC-CCA to test for schistosomiasis infection is being performed on-site for the mother and child. To test-positive mothers, a 40 mg/kg dose of PZQ treatment is offered. Test-positive children are treated with 300 mg.T4: 4th follow-up, 24 months after delivery/birth. Haemoglobin is measured for all mothers on-site using the Hemocue® system. Height and weight are measured for all children. A urine sample is being collected (≥ 25 ml) from all the women and children. In both arms, the POC-CCA test for schistosomiasis infection is being performed on-site for the mothers and children. All positive women and children are offered 40 mg/kg and 300 mg PZQ treatment, respectively.

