**Table 5 Tab5:**
[figure not shown]
Testing scheme by randomization group. The UCP-LF antibody assay will be performed at the designated laboratory on all the samples collected at T0 from the women attending the visit at both intervention and control training centres. The maternal Hb will be measured at the CSB from all the women in all the sites attending T0, T1, T3 and T4 visits. The UCP-CF CAA and the UCP-LF CAA assays will be performed at the designated laboratory on all the samples collected at T0 from all the women in all the sites and at T3 from all the children in all the sites. The POC-CCA test will be performed for all the women attending the T0, T3 and T4 visits and for all the children attending T3 and T4 visits at the CSB belonging to the intervention group. The POC-CCA test will be also performed at the designated laboratory on all the samples collected at T0 from all the women in all the sites and at T3 from all the women and children in all the sites. PCR will be performed at the designated laboratory on all the samples collected at T0 from the women attending the visit at both intervention and control training centres. Microscopy will be performed at the designated laboratory on all the samples collected at T0 from the women attending the visit at the intervention training centre (one of the two non-randomised centres)

Information on women’s health-related quality of life is collected at T0, T1, T3 and T4 in a sub-sample of women enrolled at the non-randomized centres. Information on health system resources used for TBST is collected in all the facilities by means of a simple questionnaire administered to nurses involved in the intervention.

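### The named primary comparisons use neither T0 haemoglobin nor the region strata; a cluster-valid primary model should carry both

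*Protocol article*

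**What the plan says.** Under Analysis for the primary outcomes, the maternal endpoint is handled in one sentence: "the difference in Hb 2 years after delivery will be compared between the intervention and control arms using the" t-tests. The stunting proportion "will be compared between the intervention and control arm using the chi-square tests and" t-tests. The section then adds: "Additional analyses will be performed using mixed-effects logistic and linear regression models to account for the between-cluster variation as a random effect". Those models are labelled additional, and the text lists no fixed effects for them.

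Under Data collection plan, the T0 visit entry reads: "Haemoglobin is measured on-site using the Hemocue® system, and a urine sample is being collected". It comes ahead of the on-site antigen test and the offer of treatment in the intervention arm. The Table 5 caption confirms the coverage: "The maternal Hb will be measured at the CSB from all the women in all the sites attending T0, T1, T3 and T4 visits".

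Under Randomization, the allocating centre received two lists of 20 CSBs, one per region, "which randomly allocated 10 of the sites to control and 10 to intervention arm stratified by regions". The same section concedes that blinding at CSB level is not possible.

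**The concern.** T0 Hb is a baseline measurement of the maternal endpoint itself, taken before the first treatment. Region is the factor on which the randomisation was restricted. Both are in hand, and a plain t-test or chi-square test uses neither.

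Three things are at stake.

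- **Precision for Hb.** Any part of 24-month Hb that T0 Hb predicts stays in the error term.
- **Protection against imbalance.** Only 40 units were randomised, and testing starts at T0 in intervention sites, so women enrol at a centre whose arm is already set and visible. A chance or recruitment difference in baseline Hb is plausible, and an unadjusted comparison passes it straight into the estimate.
- **A correct SE.** Once the analysis respects clusters, leaving out the stratum makes its SE larger than the stratified design warrants.

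**Working it through.** **1. The plan's own sample size (Sample size and statistical analysis).** Inputs: the control rate ("Twenty per cent of all children at the age of 2 years are stunted"), 10% in the intervention arm, alpha 0.05 (two-sided is assumed, as the side is not stated), power 80% or 90%. The unpooled formula is n per arm = (z_α/2 + z_power)² × [0.2×0.8 + 0.1×0.9] / 0.1².

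- 80%: 7.849 × 0.25 / 0.01 = 196.2, so 197 per arm and 394 in total. 394 × 1.9 = 748.6, so 749.
- 90%: 10.507 × 0.25 / 0.01 = 262.7, so 263 per arm and 526 in total. 526 × 1.9 = 999.4, so 1000.
- 4200 × 0.774 × 0.25 = 812.7 infected; 812.7 / 1.9 = 427.7 effective; power about 83%, inside the stated 80–90%.

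The figures reproduce. No Hb difference, Hb standard deviation, T0-to-24-month correlation or regional variance is given, so steps 2 and 3 rest on assumed ranges.

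**2. Gain from T0 Hb.** Adjustment multiplies the variance by 1 − ρ², taking the correlation ρ to be the same between and within CSBs. The last column shows what a comparison with 80% power would become: Φ(2.80/√(1 − ρ²) − 1.96).

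| ρ (assumed) | 1 − ρ² | SE lower by | Worth extra women | 80% power becomes |
|---|---|---|---|---|
| 0.2 | 0.96 | 2.0% | 4% | 81.6% |
| 0.3 | 0.91 | 4.6% | 10% | 83.6% |
| 0.4 | 0.84 | 8.3% | 19% | 86.4% |
| 0.5 | 0.75 | 13.4% | 33% | 89.9% |
| 0.6 | 0.64 | 20.0% | 56% | 93.8% |

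**3. Role of region.** Retained women per CSB: m = 105 × 0.774 = 81.27. The design effect of 1.9 then implies an intracluster correlation of 0.9 / 80.27 = 0.0112. This borrows the design effect assumed for stunting. If region carries a share s of the between-cluster variance, allocation within region already brings the true design effect down to 1.9 − 81.27 × 0.0112 × s.

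- s = 0: 1.900, no change.
- s = 0.25: 1.672; √(1.672/1.9) = 0.938, so the true SE is 6.2% below what an analysis ignoring region reports.
- s = 0.5: 1.444; √(1.444/1.9) = 0.872, so 12.8% below.

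At s = 0.5 a cluster-level test that omits region therefore has type I error of about 2 × [1 − Φ(1.96/0.872)] = 2 × [1 − Φ(2.248)] = 0.025.

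**4. The tests actually named.** Individual-level tests take the design effect to be 1.

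- True design effect 1.9: 2 × [1 − Φ(1.96/√1.9)] = 0.155.
- True design effect 1.444: 2 × [1 − Φ(1.96/√1.444)] = 0.103.

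**5. Simulation check.** 40 clusters in two strata, 10:10 in each, 81 women per cluster, 3000 runs per setting, no true effect.

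| Setting | Individual t-test, type I | Cluster-level, no region | Cluster-level, region | SD of arm difference, without / with region | SD adding T0 Hb |
|---|---|---|---|---|---|
| ρ 0.3, s 0 | 0.151 | 0.046 | 0.044 | 0.0481 / 0.0481 | 0.0464 |
| ρ 0.3, s 0.5 | 0.103 | 0.024 | 0.049 | 0.0422 / 0.0422 | 0.0413 |
| ρ 0.5, s 0 | 0.152 | 0.046 | 0.046 | 0.0481 / 0.0481 | 0.0423 |
| ρ 0.5, s 0.5 | 0.098 | 0.025 | 0.048 | 0.0417 / 0.0417 | 0.0361 |

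The region term does not change the spread of the arm difference; it corrects the reported SE. T0 Hb does reduce the spread, by about 2–4% at ρ = 0.3 and 12–13% at ρ = 0.5.

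**The case against.** The strongest objection is that covariates usually belong to the analysis plan, which is not shown, and that this is a condensed article. That holds for the additional mixed models. A reader might infer that they contain nothing but a cluster effect, but the text lists no fixed effects at all, not even arm, and so does not exclude T0 Hb or region. It does not hold for the primary comparisons, which are named as t-tests and chi-square tests. Under Analysis for the secondary outcomes the same article does state adjustment for other factors, so brevity does not fully explain the contrast.

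Four further inferences are tempting, and the documents do not support them.

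- **That the planned error bars are too wide.** This is true only of a cluster-valid analysis that omits region. The named tests ignore clustering, so their SE is too small. That is the larger fault in the same passage, and adding covariates to an individual-level test would not cure it.
- **That a region term would cut the true variance of the arm difference.** The 10:10 allocation within region has already done so.
- **That baseline imbalance is likely or the estimate biased.** No figure supports more than plausible.
- **That Hb is underpowered.** The sample size section assumes that stunting is the endpoint needing the larger sample.

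It is also fair that the Hb gain may be small. T0 falls in the fifth or sixth month of pregnancy, more than two years before the endpoint, so the correlation could lie at the low end of the range.

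**Conclusion.** The point holds as an inexpensive improvement to a stated method, of minor to moderate weight. The named primary tests use neither T0 Hb, measured in all women, nor the region strata of the allocation. The cost is efficiency and protection against imbalance; no bias is shown.

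Its size cannot be fixed from the documents. The SE reduction from T0 Hb is 2% to 20% for an assumed ρ of 0.2 to 0.6, with the low end quite possible. The benefit of region depends on its unknown share of the between-cluster variance: nothing at zero, and a type I error of 0.05 rather than about 0.025 at one half, in a cluster-valid analysis with the assumed design effect of 1.9. Both gains are meaningful only once the primary analysis respects the clusters.

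**What to change.** Prespecify, before the 24-month data are analysed, a cluster-valid primary model for each endpoint, in place of the t-tests and chi-square tests.

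- **Maternal Hb:** linear mixed model of 24-month Hb on arm, region and T0 Hb, with a CSB random intercept and a small-sample correction for 40 clusters.
- **Stunting:** logistic mixed model on arm and region, with a CSB random intercept and a small-sample correction.
- **Not adjusted for:** T1 Hb, T3 Hb and birth size, all of which come after treatment starts.
- **Gestational age at T0:** include only if it is recorded. The article gives an enrolment window and does not say that the value is captured.

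The unadjusted comparisons can be kept as descriptive results. The cost is a few sentences in the analysis plan and one degree of freedom for region. T0 Hb and region need no new data.
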